### Participants

Patients will be recruited in 15 centers in the United States. In all centers, patients who have not obtained satisfactory results with CMM and have not had previous major lumbar surgery will be screened for eligibility by medical record review. Consent will be obtained from potential candidates and the following screening assessments will be performed: back and leg pain on the VAS, magnetic resonance imaging (MRI), x‐rays with or without flexion‐extension views if indicated, and surgical consultation. Inclusion requires a diagnosis of chronic axial low back pain with a neuropathic component. Candidates will complete the PainDETECT questionnaire for assessment of a neuropathic pain component.^32^ The PainDETECT questionnaire will be used to guide the investigators’ assessments, but the score will not be used to automatically exclude potential subjects since the literature is mixed in terms of validating its use in the detection of neuropathic back pain.^33^ Appropriate interventional procedures should have been tried prior to enrollment with continued refractory pain.^31^ All patients were required to have an MRI‐based diagnosis and spine surgical expert opinion that surgical intervention was not indicated. If all eligibility criteria are met, demographics and baseline assessments will be collected, and subjects will be randomized.

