### Assignment of Interventions

Block randomization will be used to help maintain balance in allocation at each site. Randomization assignments will be computer generated and allocated via an electronic data capture system. Randomization is 1:1 to either the 10‐kHz SCS + CMM group or the CMM group. Figure 2 shows the study flow for both randomized groups, and Table S1 shows the timing of assessments.

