### Data Management and Statistical Analysis

Descriptive statistics will be used to summarize all subject baseline and outcome data collected during the study. Continuous variables will be summarized using means, standard deviations, and ranges. Categorical variables will be summarized in frequency distributions.

Analysis populations defined for the study include intention‐to‐treat (ITT) and per protocol (PP). The ITT population includes all randomized subjects, while the PP population includes subjects who completed the visit corresponding to the endpoint being analyzed. Note that subjects who fail the temporary trial will be included in the ITT population for the high‐frequency stimulation at 10 kHz (HF10) + CMM arm.

The primary endpoint will be evaluated with a Fisher’s exact test comparing the percentage of subjects in each group who achieve a 50% improvement in their back pain VAS score at the primary efficacy assessment in the ITT population. The following secondary endpoints will be successively evaluated (hierarchical closed test approach) at study completion in the order shown with a 0.05 significance level for difference between groups in the PP population until statistical significance is not achieved.

The comparison between HF10 + CMM and CMM alone in terms of healthcare resource use (HRU) will be made based on doctor’s office visits, emergency room visits, or hospital stays, as well as on medical tests and procedures. Medication use (opioids and medication for CLBP), work status, health status (12‐Item Short Form Survey [SF‐12]), quality of life (EuroQol 5‐Dimension, 5‐Level Instrument [EQ‐5D‐5L]) will be used in the cost‐effectiveness analysis. The change from baseline to 6‐month follow‐up will be compared for CMM vs. HF10 + CMM for all these parameters. In addition, subjects can be used as their own control comparing HRU at baseline to HRU after baseline for the HF10 + CMM arm, or pre‐ and post‐crossover for those crossing over from the CMM to HF10 + CMM at 6 months. Parametric functions (eg, Weibull, Gompertz, etc.) will be used to extrapolate from 6‐month HRU to 1, 2, and 3 years out. HRU will be associated with direct medical costs using fee schedules, Medicare claims, and peer‐reviewed literature. Changes in EQ‐5D‐5L index scores will be used to assess changes in health status and the economic value of the addition of HF10 to CMM.

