### Sample Size Calculation

Assuming a 60% responder rate in the stimulation group (10‐kHz SCS + CMM) and 36% in the control group (CMM), a sample size of 98 subjects in each group is enough to detect a significant difference with a power of 90% and a 2‐sided type I error of 0.05. Assuming a 10% attrition rate, a total of 108 subjects per group need to be randomized.

The sample size computation is based on the 2‐sided Fisher’s exact test, used for comparing 2 independent proportions, following an equal allocation randomization ratio of 1:1.

Sites will be enrolling in the study a maximum of 54 subjects (25%) per site of the total number of study subjects (216 subjects).

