### Expected Outcomes of the Study

The primary endpoint of this study provides a comparison of the percentage of subjects in each group who experience at least 50% reduction in pain intensity (as assessed by the VAS) for back pain at 3 months compared to baseline.

The secondary efficacy endpoints will be evaluated at the 6‐month time point using a hierarchical test procedure, with the hierarchy being the order in which the endpoints are listed in Table 4.

**Table 4 papr12945-tbl-0004:** Secondary Endpoints

The percentage of subjects with at least a 10‐point decrease from baseline in Oswestry Disability Index score between the treatment and control groups at 6 months Percentage change from baseline in back pain intensity (as assessed by the VAS) comparing the treatment and control groups at 6 months Proportion of subjects reporting “better” or “a great deal better” on the Patient Global Impression of Change questionnaire comparing the treatment and control groups at 6 months Health‐related quality of life evaluation as measured by the EuroQol 5‐Dimension, 5‐Level questionnaire comparing the treatment and control groups at 6 months Change from baseline in opioid equivalent medication usage in each group at 6 months*

* Based on self‐report opioid diary for record of daily opioid intake during the 7 days prior to each follow‐up visit.

The multiple observational outcomes that will be assessed (Table 5) provide significant value since they have not been collected previously in this NSRBP population. The instruments that will be used are described in Table 6. In addition to patient‐reported pain intensity, the effect of pain on daily function and sleep are assessed by the Oswestry Disability Index and the Pain and Sleep Questionnaire 3‐item index, respectively. In addition, improvement in function will be quantified with a “50‐foot walk at fastest speed” test. A composite pain and disability endpoint will allow evaluation of the proportion of subjects in each group who achieve clinically significant improvement in both pain and function.^36^

**Table 5 papr12945-tbl-0005:** Observational Outcomes

Category	Outcome*
Composite pain relief and function	Percentage of subjects in each group with ≥50% reduction in back pain plus a 10‐point reduction from baseline in the Oswestry Disability Index (ODI)

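### The primary Fisher's exact test pools sites and ignores baseline pain as a covariate although randomization is blocked by site: valid but conservative, at a modest cost in power

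*Protocol article*

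**What the plan says.** Under Assignment of Interventions, the Protocol article states: "Block randomization will be used to help maintain balance in allocation at each site". Under Participants: "Patients will be recruited in 15 centers in the United States". Back pain on the VAS is recorded at screening.

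Under Data Management and Statistical Analysis, the primary endpoint is tested in the ITT population by a Fisher's "exact test comparing the percentage of subjects in each group who achieve a 50% improvement in their back pain VAS score". No stratification and no covariate is attached to it. Results, Trial Status, reports that the interim look used the same test. Site and pain severity appear only among optional exploratory subgroup or multivariable analyses.

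Sample Size Calculation uses the same two-sided Fisher's test, "following an equal allocation randomization ratio of 1:1", at a type I error of 0.05. Interim Analysis sets the level at 0.025 at each of the two looks.

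**The concern.** Blocking within site makes site part of the design. If response rates differ between sites, which is plausible because each investigator decides what conventional management contains, a pooled comparison treats between-site variation as noise although the randomization has largely balanced it. The pooled test then rejects less often than its nominal level under the null and loses some power. Fisher's test is conservative to begin with, so the two effects add up.

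What is at stake is efficiency. Enrollment is closed at 211, so the choice of analysis is one of the few remaining ways to gain power. The article names the primary test outright, so this is a stated choice and not a detail left to an analysis plan that is not shown.

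**Working it through.** **1. The plan's own figure.** Inputs from Sample Size Calculation: a 60% "responder rate in the stimulation group", 36% in control, two-sided 0.05, power 90%. The mean rate is 0.48 and the difference 0.24.
- Uncorrected n = [1.960·√(2·0.48·0.52) + 1.282·√(0.60·0.40 + 0.36·0.64)]² / 0.24² = (1.385 + 0.879)² / 0.0576, which gives 89 per group.
- Continuity-corrected n = (n/4)·[1 + √(1 + 4/(n·0.24))]², which gives 98 per group, as stated.
- Exact enumeration of Fisher's test at 98 per group: power 90.7%.

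The figure reproduces for the planned test at 0.05.

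**2. The level that applies.** At 0.025, exact Fisher power is 84.9% with 98 and 88.1% with 108 per group. This drop comes from the change of level and has nothing to do with site or baseline pain.

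**3. Actual size of Fisher's test at nominal 0.025.** Size is the sum of Bin(x₁; n₁, p)·Bin(x₂; n₂, p) over all tables with Fisher p ≤ 0.025.
- 98 per arm: 0.0165 at p = 0.36 and 0.0181 at p = 0.48.
- Exactly equal arms are the least favourable case. With 106 and 105 (total 211), size is 0.0212 and 0.0191, and power at 60% versus 36% is 88.1%, against 86.4% with 105 in each arm. This is why the simulated Fisher power below lies near 88%.

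**4. Separating the exact test from the stratification.** A comparison of Fisher with CMH alone mixes two changes, so an unstratified chi-square test is put between them. Simulation: 15 unequal sites, blocks of 4 within site, 60% versus 36%, nominal 0.025, 5,000 runs, error about 0.4 to 0.5 point. Site SD (logit scale), site sizes and block size are assumptions; the article gives none of them. CMH statistic: [Σ(aₛ − n₁ₛmₛ/nₛ)]² / Σ[n₁ₛn₀ₛmₛ(nₛ − mₛ)/(nₛ²(nₛ − 1))], no continuity correction.

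Power (%):

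| N | Site SD | Fisher | Chi-square | CMH by site | Total gain | Part due to stratification |
|---|---|---|---|---|---|---|
| 211 | 0 | 87.8 | 90.0 | 89.2 | 1.4 | −0.8 |
| 211 | 0.3 | 88.7 | 91.3 | 90.8 | 2.1 | −0.5 |
| 211 | 0.5 | 87.9 | 90.4 | 90.9 | 3.0 | +0.5 |
| 211 | 0.8 | 89.6 | 91.6 | 93.2 | 3.6 | +1.6 |
| 190 | 0 | 84.4 | 86.7 | 86.4 | 2.0 | −0.3 |
| 190 | 0.5 | 84.0 | 86.4 | 87.5 | 3.5 | +1.1 |
| 190 | 0.8 | 85.3 | 87.5 | 90.4 | 5.1 | +2.9 |

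N = 190 is 211 less the assumed 10% attrition (211 × 0.9 = 189.9). Independent repeats agreed to within about 2 points in every cell. Under the null, CMH stayed at 2.0 to 2.7% over all runs. Fisher's test fell to 1.2 to 1.4% at SD 0.8.

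**5. How large is SD 0.8?** The logit of 0.36 is −0.575. Sites one SD either side have control rates of 1/(1 + e^1.375) = 20% and 1/(1 + e^−0.225) = 56%. That is a large spread.

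**6. Baseline VAS.** At 98 per arm and 0.05, with an assumed effect of 0.3 per SD on the logit scale and site SD 0.5: chi-square 93.2%, VAS-adjusted logistic regression 93.5%. With 0.8 per SD and site SD 1.0: 94.4% and 96.2%. The gain over chi-square is 0.3 to 1.8 points.

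**The case against.** The strongest case for the plan is that design and analysis agree: the trial was sized on the very test it will use, so Fisher's conservatism is already paid for at 0.05, and a conservative test protects a claim of superiority. This stands. The interim look has also been run with Fisher's test in an open-label trial, so replacing the primary test now, with a new pooling rule, could look like late selection of an analysis. That cost is real and has to be managed.

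Several stronger readings are tempting, and the documents do not support them:
- A reader might infer that type I error is not controlled. It is; the test falls below its nominal level, not above it.
- A reader might blame the shortfall below 90% power on the pooled test. It arises because Interim Analysis tests at 0.025 while Sample Size Calculation uses 0.05.
- A reader might say that baseline pain is not used at all. Response is defined by the reduction "for back pain at 3 months compared to baseline", so baseline enters the endpoint; it is only not a covariate.
- A reader might count the lack of a baseline-adjusted model or a confidence interval as a gap. Table 4 names "Percentage change from baseline in back pain intensity (as assessed by the VAS) comparing the treatment and control groups at 6 months" as an endpoint but states no model for it, and such models may stand in the analysis plan, which is not shown.

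**Conclusion.** The point holds as a matter of efficiency, not validity. The pooled Fisher's test neither stratifies by site nor adjusts for baseline VAS, and it uses less than its nominal level: about 1.7 to 1.8% of 2.5% at 98 per arm, nearer 2% when the arms differ slightly in size, and about 1.4% or a little less if site effects are large.

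Moving to a site-stratified CMH test gains about 1.5 to 4 power points at N = 211 and 2 to 5 at N = 190, over assumed site SDs of 0 to 0.8. Up to SD 0.5, most or all of this comes from leaving the exact test, and stratification contributes about a point at most. At SD 0.8 stratification adds about 1.5 to 2.5 points (2.9 in the N = 190 run), and the two parts are then of similar size. The true between-site variation, block size and site sizes are not in the article, so where the trial lies in this range is unknown.

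**What to change.** Before final unblinding, and without access to aggregate results by arm, specify one of these as the primary test at the final look:
- a CMH test stratified by site, with a fixed rule for pooling small sites; or
- logistic regression on arm, site and baseline VAS, reported as a standardized risk difference with a 95% confidence interval.

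Report the pooled Fisher's test as a sensitivity analysis. The 0.025/0.025 split stays valid whichever test is used at the final look, because 0.025 + 0.025 = 0.05 bounds the overall error without any assumption about how the two tests are related.

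The cost is an amendment to the analysis plan and a pooling rule; no further patients, visits or data are needed. The downside is a change of primary test after an interim look that used Fisher's test. The amendment should be dated and should record that those who made it knew only the interim recommendation, consistent with the blinding to aggregated results described under Limitations. The mismatch between 0.025 and 0.05 needs its own correction; this change does not replace it.

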Observational outcomes will be compared between groups using statistical tests appropriate to the type of outcome.

Additional exploratory analyses may be performed to examine the consistency of results in selected subgroups (eg, based on gender, study site, age, body mass index, mental health [based on Patient Health Questionnaire (PHQ‐9) response], pain duration, pain severity, etc.). These analyses may also take the form of multivariable analyses, where the contributions from membership in multiple subgroups to a study endpoint are simultaneously estimated.

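### The 6-month cost-effectiveness contrast is set as change from baseline with no baseline adjustment named; adding the baseline value as a covariate is a free gain in precision (low severity)

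*Protocol article*

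**What the plan says.** In the protocol article, the health-economic paragraph of Data Management and Statistical Analysis lists healthcare resource use, medication use, work status, SF-12 and EQ-5D-5L, and then sets the contrast: "The change from baseline to 6‐month follow‐up will be compared for CMM vs. HF10 + CMM for all these parameters". For the economic evaluation it adds: "Changes in EQ‐5D‐5L index scores will be used to assess changes in health status and the economic value of the addition of HF10 to CMM". The paragraph names no test, model or covariate.

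The gated secondary endpoints are described elsewhere. They are tested "in the order shown with a 0.05 significance level for difference between groups in the PP population", in the order of Table 4. EQ-5D-5L is fourth: "Health‐related quality of life evaluation as measured by the EuroQol 5‐Dimension, 5‐Level questionnaire comparing the treatment and control groups at 6 months". Opioid use is fifth: "Change from baseline in opioid equivalent medication usage in each group at 6 months". SF-12 is not gated. It is an observational outcome, for which the article says: "Observational outcomes will be compared between groups using statistical tests appropriate to the type of outcome".

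On allocation, Assignment of Interventions says: "Block randomization will be used to help maintain balance in allocation at each site".

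**The concern.** A plain comparison of change scores fixes the slope on baseline at 1. When the baseline value and the 6-month value correlate at less than 1, that slope is too steep. The arm that starts lower by chance tends to show the larger change through regression to the mean, and this adds noise to the estimated treatment difference. Putting the baseline value in as a covariate removes that noise, and the baseline values are collected in any case.

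The clearest stake is the incremental utility. The article bases economic value on changes in the EQ-5D-5L index, so noise from the baseline enters the effect side of the cost-effectiveness analysis directly. There is a second, conditional stake. If the fourth gated endpoint were tested in the same unadjusted way, its power would be lower than it need be, and a miss there would end the sequence before opioid use.

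**Working it through.** **The plan's own figure.** The only sample size stated is for the primary endpoint: 60% versus 36%, 90% power, two-sided 0.05, Fisher's exact test. The normal-approximation formula gives 89 per group without and 98 with continuity correction, and exact Fisher power at 98 per group is 90.7%. The stated 98 is reproduced. The article states no power for EQ-5D-5L, SF-12 or medication use.

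**Inputs for the check**
- Evaluable subjects per arm: 98 (Sample Size Calculation).
- Two-sided alpha: 0.05 (Data Management and Statistical Analysis).
- Difference: 0.08, the EQ-5D-5L MCID in Table 6. It is used as an illustration; the article does not call it a design effect.
- Assumptions that are not in the article: cross-sectional SD of 0.18 to 0.25, equal at both visits, and rho of 0.3 to 0.7.

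**Variance.** Per subject, an unadjusted change has variance 2(1 − rho)·SD². The baseline-adjusted 6-month value has residual variance (1 − rho²)·SD². Since 1 − rho² = (1 − rho)(1 + rho), the ratio of adjusted to unadjusted is (1 + rho)/2, that is 0.65, 0.75 and 0.85 at rho 0.3, 0.5 and 0.7. The unadjusted variance is therefore 2/(1 + rho) times the adjusted one, for example 2/1.5 = 1.33 at rho 0.5.

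**Power.** At SD 0.20 and rho 0.5, the SD of change is 0.20 × √(2 × 0.5) = 0.200 and the adjusted SD is 0.20 × √(1 − 0.25) = 0.173. Noncentral-t power for a difference of 0.08 with 98 per arm:

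| SD | rho | Unadjusted change | Baseline-adjusted | Gain (points) |
|---|---|---|---|---|
| 0.18 | 0.3 | 74.4% | 90.1% | 15.6 |
| 0.18 | 0.5 | 87.2% | 94.7% | 7.5 |
| 0.18 | 0.7 | 97.9% | 99.1% | 1.2 |
| 0.20 | 0.3 | 65.3% | 83.2% | 17.8 |
| 0.20 | 0.5 | 79.6% | 89.6% | 10.0 |
| 0.20 | 0.7 | 94.9% | 97.4% | 2.5 |
| 0.25 | 0.3 | 47.0% | 64.7% | 17.7 |
| 0.25 | 0.5 | 60.6% | 73.0% | 12.4 |
| 0.25 | 0.7 | 82.1% | 87.7% | 5.7 |

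Gains are taken before rounding. With about 95 per arm (211 × 0.9 / 2 = 95), the SD 0.20, rho 0.5 case is 78.3% versus 88.6%.

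**Effect on the incremental utility.** At SD 0.20, one standard error of the baseline difference is 0.20 × √(2/98) = 0.029. A baseline difference of that size moves the unadjusted change difference by (1 − rho) × 0.029, that is by 0.020, 0.014 and 0.009 at rho 0.3, 0.5 and 0.7. Against 0.08 this is about 25% down to 11%. It is as likely to favour one arm as the other.

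**The case against.** The strongest reply is that the article never calls the change comparison raw or unadjusted. An ANCOVA on change with baseline as covariate fits the sentence and gives the same treatment effect as an ANCOVA on the 6-month value. Models and covariates are commonly left to the SAP, and the Trial Status section confirms that a SAP exists; it is not shown here. This stands. The article does not establish that baseline is ignored, and the missing model is not an error in itself. What remains is that the contrast is stated in writing as change from baseline, and that a short clause would rule out its weaker form.

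A reader might go further and infer that power is lost at the fourth step of the hierarchy, blocking the fifth. The documents do not support this. The sentence sits in the health-economic paragraph and does not define the gated tests, and Table 4 describes the EQ-5D-5L endpoint only as a group comparison at 6 months, without mentioning change.

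Two other inferences also go too far. Chance imbalance does not bias the result: under randomization the change-score difference is unbiased, and the imbalance is already reflected in its standard error. Leaving out the site blocks is not a demonstrated fault either: the article does not say that site is ignored, doing so would usually cost some precision without biasing the comparison, and no figure for that cost can be derived from the article.

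**Conclusion.** The point holds as a low-severity improvement that costs nothing in data, not as an error in the plan. If the stated 6-month change comparison is run unadjusted, its variance is 18% to 54% higher than it need be (2/1.7 = 1.18 at rho 0.7; 2/1.3 = 1.54 at rho 0.3), and the incremental utility carries random error that could be removed. The power gain from adjustment runs from about 1 to 18 points, with 79.6% versus 89.6% in the middle case. The size depends on an assumed SD and correlation and on borrowing the MCID as the difference, so the article alone cannot narrow it. The conclusion covers the continuous cost-effectiveness inputs; it reaches the gated EQ-5D-5L endpoint only if the SAP analyses that endpoint in the same way.

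**What to change.** Keep the existing sentence, because it also covers healthcare resource use, work status and other medication, and add to it:

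*For continuous measures (EQ-5D-5L index, SF-12 PCS and MCS, daily opioid dose) the comparison will be adjusted for the baseline value of the same measure by ANCOVA, with a rank-based or robust version for opioid dose. The baseline-adjusted EQ-5D-5L difference will be used as the incremental utility.*

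Raw change can stay as a descriptive summary. Adjustment for site is optional. If the SAP already specifies baseline adjustment, a cross-reference is enough. The SAP should also say whether the gated EQ-5D-5L endpoint uses the same model.

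The cost is one clause of analysis wording, one degree of freedom, and a model-based difference to report in place of a raw one. No further data are needed.
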